## Abstract

**Background:**

One of the most traumatic injuries a child can experience is a severe burn. Despite improvements in medical treatments which have led to better physical outcomes and reduced mortality rates for paediatric burns patients, the psychological impact associated with experiencing such a traumatic injury has mostly been overlooked. This is concerning given the high incidence of psychopathology amongst paediatric burn survivors.

**Objectives:**

This project will aim to pilot test and evaluate a co-designed trauma-focused intervention to support resilience and promote positive mental health in children and adolescents who have sustained an acute burn injury. Our first objective is to collect pilot data to evaluate the efficacy of the intervention and to inform the design of future trauma-focussed interventions. Our second objective is to collect pilot data to determine the appropriateness of the developed intervention by investigating the changes in mental health indicators pre- and post-intervention. This will inform the design of future interventions.

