## Objectives

The project seeks to further elucidate sources of stress and trauma that accompanies a burn injury and to develop a much-needed trauma-focused psychosocial intervention through co-design to maximise its impact in this population. We also seek to pilot test and evaluate this intervention to support resilience and promote positive mental health recovery in children and adolescents who have sustained a burn injury. The specific objectives of the intervention are to:

Undertake preliminary analyses to explore the association of mental health indicators with burn characteristics and demographics.Collect pilot data to determine the appropriateness of the developed intervention by investigating the changes in mental health indicators pre- and post-intervention.

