## Methods

### Study design

This study is a non-randomised, pre-post, cohort study which seeks to determine the potential effects of a psychosocial intervention. We use convenience sampling, with data collected from age-appropriate questionnaires at four time points: Time 1 (T^1^): baseline assessments; Time 2 (T^2^): post intervention assessments; Time 3 (T^3^): 6-month follow up assessments; Time 4 (T^4^): 12-month follow up assessments. Randomisation and blinding are not relevant in this pilot study due to the single intervention arm, where intervention’s absolute effect on the participants across time is the primary interest to determine the appropriateness of the intervention content [37].

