Eligible participants who are approached will be given a Participant Information Sheet (PIF), will have the project explained verbally by the researcher, and will be given the opportunity to ask any questions. Full informed consent will ensure that the caregiver understands the adequate dosage of intervention that needs to be provided to see sufficient therapeutic gains and that the caregiver provides commitment (and that of the child’s) to the process of intervention in order to minimise attrition. Informed consent will be sought from young people aged 12 years and older and their caregivers via REDCap [39]. Children aged 6–11 years old will be provided with an age-appropriate verbal explanation of the study by the researcher. The researcher who conducts the consenting process will also sign a consent form, confirming they have checked participants’ identity and have given a verbal explanation of the study to the participant. In addition to the information obtained during T^1^ (baseline assessments), caregivers will be asked to consent to their child’s medical records (obtained from the Child Adolescent Health Service [CAHS] database) being used in the current study. Specifically, the PIF asks caregivers if the researchers can access the following information about their child: location of the burn, severity of the burn, date of burn event, time spent in hospital following burn. This information will be used to further describe the demographics of study participants.

*Sample size*. There will be an active recruitment process until the proposed sample size of 40 children has been met. This is a novel intervention for paediatric burn patients, and thus similar outcome analyses have not been published, making sample size estimation difficult. Sample size calculations are not required for all pilot studies, however they must be representative of the target study population and inclusion criteria [40]. Thus, this pilot study has a sample size of 40 children, that is representative of the paediatric burns population at our study site and participant eligibility criteria. Having a sample size of 40 children will ensure this study is feasible and accounts for a 20% attrition rate.

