### Instruments

During baseline assessment (T^1^), a demographic questionnaire will be administered to adolescents (12–17 years old) and all caregivers to capture their age, gender, and any mental health conditions they or their child have been diagnosed with prior to and after the child’s burn injury. For children aged 11 years and younger, caregivers will capture this information on their behalf. The potential effects and feasibility of our intervention will be assessed via the selection of measures from the screening procedure with the aim of determining whether the current content of the intervention can cause change in mental health outcomes for participants [47]. Children aged 8–17 years (self-report) and caregivers (caregiver report and self-report) will complete a range of screening tools at pre- and post-intervention (T^1^ and T^2^ respectively), as well as at 6- and 12-months post-intervention (T^3^ and T^4^ respectively), which will be used as outcome measures of the intervention and to assess mental health (Table 2).

**Table 2 pone.0294237.t002:** Child and caregiver screening measures used in The Wellbeing Program.

Construct	Measure	Participants age range	Reliability	Items (number and response procedure)	Additional information
**Internalising and externalising behaviours**	The Strengths and Difficulties Questionnaire (SDQ) [53].	Caregiver report: On behalf of children aged 6–17 years Self-report: Children aged 11–17 years only	Test-retest reliability rho = .62 and internal consistency α = .73	25 items	The SDQ is a screening tool that can be used as a treatment outcome measure for children and adolescents [53]. The SDQ asks about attributes such as emotional symptoms (5 items), conduct problems (5 items), hyperactivity or inattention (5 items), peer relationship problems (5 items) and prosocial behaviour (5 items) [53].

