## Data preparation and statistical analysis

All screening measures will be thoroughly checked by two research members to ensure all applicable questions have been answered. Missing data will be imputed where necessary, with the method depending on attrition rates and the degree of missing data. Scoring of all screening measures will be completed in REDCap or on the measure’s online software through syntax, which will minimise the risk of data entry errors. The quantitative data will be analysed using Stata data analysis software to determine relationships between our mental health measures and significant independent variables such as demographics (e.g., birth sex, age, age at injury) and injury characteristics (e.g., nature of the burn, size, and location) using basic descriptive analyses (Objective 1). This software will also be used to determine if the measures provide meaningful information on whether our intervention improves the mental health of children and young people who have survived a burn injury. Improvements in child and caregiver mental health (via SDQ, CBCL, YSR, STAI, STAI-CH, CPSS-5, PCL-5, PSS-10, PSS and CD-RISC) pre- (T^1^) and post-intervention (T^2^, T^3^, T^4^) will be investigated (Objective 2). Normality of all data will first be tested using Shapiro-Wilk’s test, which is ideal for sample sizes of less than 50 [76]. We will also utilize graphical presentation of the data (e.g., boxplots and histograms) to aid in determination of normality in the data [76]. If the data is normally distributed, then dependent t-tests will be employed to determine change in measure scores (e.g., changes in anxiety scores). If the data is not normally distributed, then we will employ the Wilcoxon signed-rank test instead.

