### Strengths and limitations

The aim of this intervention is to support resilience and promote positive mental health in children and adolescents who have sustained an acute burn injury and significantly benefit routine care. Participation in this study has the potential to equip children with skills and strategies to cope during distressing situations relating to their burn injury and in the future. Since this is not a clinical intervention, rather a support program to assist families in recovery, this program can be delivered by someone without a clinical background. However, the person administering the screening tools must be suitability qualified or administer tools under supervision of a clinical psychologist or psychiatrist. Furthermore, the generalisability and accessibility of this intervention allows this intervention to be adapted for other medical trauma populations and can be accessed by children living in rural and remote areas.

Due to the nature of this pilot study, a hypothesis is not tested and therefore safety and efficacy are not evaluated [80]. Participation in this pilot research will provide valuable information for the evaluation of the intervention and will provide modifications in the planning and design of a larger efficacy trial to determine the magnitude of the effect that the intervention has on child and caregiver mental health [47]. This would also eliminate the potential influence of confounders in current protocol by means of randomization and blinding. The present protocol is limited by timeframe and funding and thus convenience sampling was deemed to be most feasible. This limits the generalisability of the study’s findings to other populations outside of Western Australia. However, progression into a randomised clinical trial may alleviate this concern.

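### The article both promises and disclaims an efficacy evaluation, and its unranked tests of change in a single arm let a chance improvement be reported as efficacy

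*Protocol article*

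**What the plan says.** The article describes the purpose of the study in several places, and the descriptions differ.

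- Abstract, Objectives: "Our first objective is to collect pilot data to evaluate the efficacy of the intervention".
- Objectives section: the first of two objectives is instead to "Undertake preliminary analyses to explore the association of mental health indicators with burn characteristics and demographics". The second is to judge appropriateness from change before and after the intervention. Neither is efficacy.
- Study design: a single arm, in which the intervention's "absolute effect on the participants across time is the primary interest". No instrument, informant or time point is attached to that interest.
- Instruments: the measures serve the aim of "determining whether the current content of the intervention can cause change in mental health outcomes for participants".
- Data preparation and statistical analysis: ten instruments are listed side by side, with change from T1 examined at T2, T3 and T4. "If the data is normally distributed, then dependent t-tests will be employed to determine change in measure scores"; otherwise the Wilcoxon signed-rank test is used. The same section counts improved mental health among the results that will show whether the design suits a future roll-out.
- Strengths and limitations: "Due to the nature of this pilot study, a hypothesis is not tested and therefore safety and efficacy are not evaluated".

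**The concern.** A reader cannot tell whether the study evaluates efficacy. The abstract says it does, the limitations say it does not, and the analysis section supplies tests that could serve the first reading.

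The design cannot support that reading. Children qualify if they attended the burns centre in the previous 12 months, and they are followed for 12 months after the intervention with no comparison group. Change from T1 therefore mixes any intervention effect with natural recovery. The limitations concede that confounding would be dealt with by randomisation and blinding in a later trial.

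No outcome leads. If the analysis is carried out as written, a nominally significant improvement on any scale, from any informant, at any follow-up, could be presented as meeting the abstract's first objective and used in support of roll-out.

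**Working it through.** **The plan's own figures.** No power calculation, significance level or number of tests is given, so there is no error rate to reproduce. The sample size is 40 children with 20% attrition: 40 × 0.8 = 32 completers.

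**Counting the tests.** Inputs are Table 2 (instruments, informants, age ranges) and the Instruments text, which gives every measure three comparisons with T1 except the SDQ, which has two because it is not given at T2.

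- One test per named instrument and follow-up: 9 × 3 + 1 × 2 = 29.
- One score per instrument–informant pair. There are 14 pairs, because the SDQ, STAI, PSS-10 and CD-RISC each have two informants: 12 × 3 + 2 × 2 = 40.
- As above, with state and trait anxiety scored separately for the three STAI/STAI-CH pairs: 2 × 2 (SDQ) + 3 × 2 × 3 (anxiety) + 9 × 3 (others) = 4 + 18 + 27 = 49.

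The range at total-score level is 29 to 49. Subscales or age strata would raise it.

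**Chance of at least one nominally significant improvement when nothing has changed.** Two-sided 0.05 is assumed, so each test has probability 0.025 of a false result in the favourable direction.

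*Independent tests:* 1 − 0.975^k.
- k = 29: 52.0%; expected number 29 × 0.025 = 0.7.
- k = 49: 71.1%; expected number 49 × 0.025 = 1.2.

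*Common correlation ρ between all test statistics:* 1 − ∫ Φ((1.96 − √ρ·u)/√(1 − ρ))^k φ(u) du.

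| k | ρ = 0.5 | ρ = 0.7 |
|---|---|---|
| 29 | 25% | 17% |
| 49 | 31% | 20% |

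*Structured simulation, k = 49:* 32 children, ages assumed uniform over 6–17, each instrument given only to its age range. Two follow-ups on one score correlate 0.5 through the shared baseline, and r is the assumed correlation between different scores at the same occasion. The chance of a favourable false positive is 63% at r = 0, 53% at 0.3, 46% at 0.5 and 36% at 0.7. These exceed the common-correlation figures because different scores at different follow-ups correlate only r/2 and some instruments are answered largely by different children.

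**Comparison.** A single prespecified test would carry 2.5% in the favourable direction.

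**The case against.** The strongest reply is that the article already contains its own restraint. The limitations leave the size of effect to a larger efficacy trial. Several sections speak only of potential effects, and Study design ties the purpose to whether the content is appropriate. The analysis section says the software will show whether the measures are informative about improvement, which is weaker than deciding that improvement occurred. Adherence, attrition, recruitment uptake, session ratings and individual-change statistics are also planned. Handling of multiplicity may sit in an analysis plan that is not shown.

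Much of this stands. It lowers the risk and rules out reading the roll-out decision as resting on p-values alone. The absence of a multiplicity method is not counted here as a fault. But the contradiction is between statements in the article itself, and no separate plan can make both true. The disclaimer cannot do its work while the abstract, the causal wording under Instruments and the tests remain as they are.

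Two stronger readings should be resisted. A reader might infer that the protocol prescribes 49 significance tests; it does not, because 49 is a derived upper count at total-score level. A reader might also quote the two-sided chance of any significant result with 49 tests: 92% if independent, 62% at a common correlation of 0.5 and 40% at 0.7. Those figures include chance deteriorations, whereas the harm at issue is a chance improvement, for which the corresponding figures are 71%, 31% and 20%.

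**Conclusion.** The concern holds. The article's stated purposes contradict each other, and the design cannot deliver the one in the abstract.

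The size of the risk depends on the model. The chance of at least one spurious improvement runs from about 17% (29 tests, common correlation 0.7) to 71% (49 independent tests), with 46% and 36% from the structured simulation at between-score correlations of 0.5 and 0.7. Every value is well above 2.5%. The figures rest on an assumed two-sided 0.05, a derived test count, assumed correlations and, for the simulation, assumed uniform ages.

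It might be inferred that a particular instrument must be made primary. The documents do not compel that: once significance-based claims are dropped, the choice of a lead outcome is a preference. Because the article's own limitations already disclaim efficacy, this is a point that should be fixed, not one that invalidates the study.

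**What to change.** 1. In the abstract, replace the efficacy objective with the two objectives of the Objectives section plus feasibility. Under Instruments, reword the causal aim so that it speaks of describing change. Both then agree with Strengths and limitations.
2. In the analysis section, report mean change with a 95% confidence interval for every instrument, informant and time point. Label all tests exploratory, and make no significance-based statement that the intervention improves outcomes.
3. If the sponsor keeps any test-based conclusion, name one lead instrument, informant and time point beforehand. The choice is the sponsor's. Caregiver-report CBCL is one candidate, because it covers ages 6–17 at all four time points.

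The cost is small. No new data or participants are needed, but the paper gives up significance-based claims that the design cannot support. The Ethics section requires committee approval of protocol modifications. The change should be in place before analysis begins, which the timeline sets after all T2 data are in.

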**Methods:**

This pilot intervention study will recruit 40 children aged between 6–17 years who have sustained an acute burn injury and their respective caregivers. These participants will have attended the Stan Perron Centre of Excellence for Childhood Burns at Perth Children’s Hospital. Participants will attend a 45-minute weekly or fortnightly session for six weeks that involves building skills around information gathering, managing reactions (behaviours and thoughts), identifying, and bolstering coping skills, problem solving and preventing setbacks. The potential effects and feasibility of our intervention will be assessed through a range of age-appropriate screening measures which will assess social behaviours, personal qualities, mental health and/or resilience. Assessments will be administered at baseline, immediately post-intervention, at 6- and 12-months post-intervention.

**Conclusion:**

The results of this study will lay the foundation for an evidence-based, trauma-informed approach to clinical care for paediatric burn survivors and their families in Western Australia. This will have important implications for the design of future support offered to children with and beyond burn injuries, and other medical trauma populations.

## Introduction

### Psychological and psychosocial outcomes following a paediatric burn injury

Burn injuries are one of the leading causes for hospitalisation amongst Australian children and adolescents [1]. These injuries are profoundly traumatic for children, due to the pain of the acute injury, subsequent laser and scarring treatments, and procedures that continue across prolonged periods [2–4]. Although improvements in medical treatments have led to better physical outcomes and reduced mortality rates for paediatric burns patients, the psychological impact associated with experiencing such a traumatic injury has mostly been overlooked, particularly within the routine care context [5–9]. This is despite a wealth of studies showing that children and adolescents who experience a burn injury are at increased risk for both short- and long-term psychopathology [10].

Although some children who sustain a burn injury do not experience later mental health difficulties, others can experience a range of psychosocial problems. In a recent systematic review, Woolard et al [4] found that this population are highly vulnerable to a range of mental health problems such as anxiety, traumatic stress symptoms, depression, and emotional issues. Although there was variability with some mental health outcomes such as depression, emotional issues, self-esteem, and quality of life, the authors found that the most consistently reported mental health concerns in children who have sustained a burn injury were increased anxiety symptoms and traumatic stress [4]. It has been reported that children who have sustained a burn injury are at greater risk of having an anxiety disorder (28%) compared to uninjured children (6.9%) [4, 11, 12]. Factors that have been associated with high rates of anxiety in paediatric burns patients include hospitalisation, pain related to medical procedures, the injury itself, wound dressings, procedural fear, appearance concerns, and gender (higher anxiety observed in female children) [4]. Disruption to schooling and other lifestyle factors such as missing out on sporting activities have also shown to have a big impact on the child [13]. Furthermore, Woolard et al [4] found mixed results regarding the association between severity of the burn and later psychosocial outcomes [4]. For example, anxiety and depression were found to be associated with pain severity and intensity, whereas other psychological outcomes showed no direct association with severity [4]. However, another study found that burn size did not impact mental health outcomes and did not necessarily impact perception of pain [14]. Bakker et al (2013) examined stress symptoms in children who have sustained a burn injury and found that approximately 8% of children required treatment for an Acute Stress Disorder (which is comparable to 6% to 30% of people who have experienced other types of trauma [15–18]) [10]. Further studies with paediatric burn patients have examined chronic stress symptoms and found that 11.7% of children [19] and 13.2% of toddlers [20], met the full criteria for Post-Traumatic Stress Disorder (PTSD). Concerningly, these rates increase to anywhere between 15% to 66.7% when looking at subthreshold levels of stress (at least one cluster of trauma-based stress symptoms such as re-experiencing the event, avoidance, emotional numbing or increased arousal) [19].

In addition to the trauma experienced by the child, the impact of a paediatric burn on the family can also be traumatic [21]. A commonly reported outcome in caregivers following their child’s injury is feelings of guilt associated with the injury [21, 22]. Feelings of guilt have been positively associated with traumatic stress and anxiety in caregivers, which can be maintained for many years after the injury event [23]. Some families experience increased parenting stress and poorer family functioning due to a barrage of hospital stays or appointments, providing dressing changes and managing scar treatments [19]. Given this increased carer burden, families of paediatric burn patients can experience considerable distress that can have a negative impact on the family’s overall functioning [22]. Research has found that a high proportion of caregivers with a child who has sustained a burn injury were diagnosed with anxiety (33% to 69%) and depression (22% to 44%) [22], which is concerning given that parental anxiety is a risk factor for anxiety disorders in their offspring [24].

It is important to recognise that not all paediatric burn patients and their families experience negative mental health outcomes post-injury. To gain an understanding of why some patients adapt better to the challenges of sustaining a burn injury than others, Woolard et al [25] conducted a systematic review and meta-analyses to identify the barriers, enablers and interventions that lead to psychological recovery after sustaining a burn. This study found that having strong social support, (i.e., positive relationships with family, friends, and community) as well as spirituality were both key factors that enabled resilience and Post Traumatic Growth (PTG) in burn patients. Resilience was found to be enabled through personality factors such as optimism, and positive skills-based factors including problem-solving, social competence and autonomy [25]. Additionally, PTG was facilitated by coping mechanisms (e.g., acceptance of the injury), narrative restructuring to positively reframe the accident, and extraversion [4, 25]. This review identified the need for more research in the underlying mechanisms of both resilience and PTG, especially in child and adolescent populations who make up a large demographic for burn injuries [25].

